### Endpoints

The primary endpoint is the incidence of postoperative complications (Clavien–Dindo classification grade ≥ III) [35]. The rate of severe postoperative complications in all eligible patients will be investigated, and risk factors affecting them will be determined.

A key secondary endpoint is the incidence of intraoperative vascular injury around the SMV. The rate of intraoperative vascular injury around the surgical trunk in all eligible patients will be investigated, and risk factors affecting it will be extracted.

Other secondary endpoints include the incidence of postoperative complications (Clavien–Dindo classification grade ≥ II), 5-year overall survival, recurrence-free survival, and other short- and long-term outcomes (operative time, blood loss, conversion rate, degree of lymph node dissection, intraoperative complication rate, reoperation rate, R0 resection rate, local recurrence rate in the whole cohort and by stage, and incidence of bowel obstruction and herniated abdominal wall scarring). Factors influencing the above endpoints will be determined for all eligible patients. Furthermore, comparisons will be made between each subgroup, as shown in Table 1.

**Table 1 Tab1:** Secondary endpoints

1. Short-term results by approach (a. Medial approach vs. retroperitoneal approach; b. Medial approach vs. cranial approach; c. Retroperitoneal approach vs. cranial approach; a–c for laparoscopic surgery and robotic surgery, respectively)
2. Short-term results of robot-assisted and laparoscopic surgery (Comparison in all approaches, medial approach, retroperitoneal approach, and in each ASA-PS, respectively)
3. Short-term results by degree of lymph node dissection (D2, D3v, D3a)
4. Long-term results by approach, robot or laparoscopy, and degree of dissection
5. Impact of experience on short-term and long-term outcomes after the surgery performed by the surgeons before obtaining board certification in gastrointestinal surgery (including the investigation by each approach, robot/laparoscopy, and degree of lymph node dissection)
6. Impact of surgeons’ case volume prior to obtaining board certification in gastrointestinal surgery on short- and long-term outcomes following robot-assisted procedures
7. Impact of the participation of Endoscopic Surgical Skill Qualification-certified surgeons in surgery and their role in the procedure on short- and long-term outcomes
8. Impact of anastomosis method on short- and long-term outcomes

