
### Target number of cases

The target number of cases for the study is 2,000; nevertheless, we aim to recruit as many cases as possible within the study period.

The rationale for setting the target number of cases is described below.

The postoperative complication rate (grade ≥ III) of laparoscopic surgery in all patients with colon cancer in a Japanese randomised controlled trial (RCT) (JCOG0404) was 4.6% [3]. The postoperative complication rate (grade ≥ III) for laparoscopic CME of right colon cancer in a Norwegian RCT was 6.1% [10]. Based on these reports, we calculated that a sample size of approximately 2,000 cases is required to achieve a postoperative complication rate (grade ≥ III) of 5% and a 95% confidence interval within ± 1.0% based on the binomial distribution in this study.

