Secondary endpoints: Summary statistics for patient background and other surgical outcomes will be calculated. A multivariate logistic regression or multiple regression analysis will be performed using the factors listed in the survey items that may influence outcomes. A random-effects model will be used to account for differences between the centres. The main endpoint for short-term outcomes for each subgroup is postoperative complications (Clavien–Dindo classification grade ≥ II), and group comparisons will be conducted after propensity score matching (differences between groups will be tested using Student’s t-test and the χ^2^ test) and logistic regression to identify confounders. Multiple regression analysis will be used to analyse continuous variables. A random-effects model will be used to account for the differences between institutions. The Kaplan–Meier method will be used to plot cumulative late complication curves, local and overall recurrence-free survival curves, and overall survival curves for long-term outcomes. To account for confounding factors, a multivariate Cox regression analysis will be performed using preoperative and postoperative factors that may contribute to recurrence and late complications, and risk factors will be examined. In addition to regression analysis of factors, each factor will be discussed from clinical and medical perspectives to reach a combined perspective.

The number of experienced cases will be added to the factors in the multivariate analysis to examine their effect on the outcome. The correlation of the number of cases experienced and outcomes (operation time and blood loss) with the learning curve will be evaluated using the moving average method and the cumulative sum curve.

Statistical significance will be set at *p* < 0.05.

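### Logistic regression is given the task of identifying confounders for the technique comparisons, which it cannot do; they should be prespecified from preoperative items

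*Protocol article*

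**What the plan says.** The Endpoints section announces that "comparisons will be made between each subgroup, as shown in Table 1". Table 1 then lists contrasts by approach (separately for laparoscopic and robotic surgery), robot versus laparoscopy, extent of dissection, anastomosis and others.

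The Statistical analysis section, under secondary endpoints, names Clavien–Dindo grade II or higher as the main short-term outcome for these contrasts. It says that "group comparisons will be conducted after propensity score matching" and "logistic regression to identify confounders". A little earlier it takes the regression factors from the collected data, "using the factors listed in the survey items that may influence outcomes". Random effects for institution are planned, as is a clinical discussion of each factor. The section closes with a general statement: "Statistical significance will be set at" p < 0.05.

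For the long-term outcomes the same section describes a multivariable Cox model whose stated purpose is to allow for confounding. That is a statement of adjustment, not of identification.

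**The concern.** These contrasts are not randomised, so confounding is the main threat to them. A confounder must be related to the outcome, must be related to the choice of technique, and must not be a consequence of that choice. A logistic model for complications addresses only the first condition. If the phrase instead refers to the propensity model, that model addresses only the second. Neither can identify confounders, so the article states a purpose that the method cannot serve.

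The wording opens two risks.

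- **Wrong variables let in.** The data listed under Observation, investigation data, and methods include operation time, blood loss, open conversion and intraoperative vascular injury. These follow the choice of technique and may be part of how it acts. An outcome model would flag them if they predict complications, and adjusting for them could remove part of the effect under study.
- **Right variables left out.** If flagging were decided by significance, weak confounders would often be missed, most of all in the small within-platform contrasts.

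The Background says that data collection was structured to answer which approach, platform, dissection level and anastomosis is safest. The wording therefore bears on questions that the study was built to inform.

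**Working it through.** **The plan's own figure.** "The target number of cases for the study is 2,000", for a 95% interval within ±1.0 point at a grade III or higher rate of 5%. At n = 2,000 the Wald half-width is 1.96 × √(0.05 × 0.95 / 2,000) = 0.96 points. The exact interval is 4.09–6.05%, a half-width of (6.05 − 4.09)/2 = 0.98 points. The figure reproduces. It concerns the primary incidence only; the technique contrasts have no sample size of their own.

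**Size of the contrasts.** The Discussion expects nearly equal laparoscopic and robotic numbers, so about 1,000 each. A pairwise approach contrast within one platform has at most about 1,000 patients, and fewer after matching.

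**Inputs not in the document (assumptions).** Grade II or higher rate 10–20%; a binary factor present in 30%; outcome odds ratio (OR) 1.2–2.0; two-sided 0.05 used as the rule for keeping a factor.

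**Chance that one factor is flagged.** With overall rate r, outcome rates p0 and p1 without and with the factor, and n0 and n1 patients:

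power = Φ[(p1 − p0 − 1.96·SE0) / SE1], where SE0 = √[r(1 − r)(1/n0 + 1/n1)] and SE1 = √[p0(1 − p0)/n0 + p1(1 − p1)/n1].

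Example: N = 600, r = 10%, OR 1.5. Then n0 = 420 and n1 = 180, with p0 = 0.0884 and p1 = 0.1270 (check: 0.7 × 0.0884 + 0.3 × 0.1270 = 0.100). SE0 = 0.0267 and SE1 = 0.0284, so power = Φ[(0.0386 − 0.0523)/0.0284] = Φ(−0.48) = 31%.

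| N | OR 1.2 | OR 1.3 | OR 1.5 | OR 2.0 |
|---|---|---|---|---|
| 2,000 | 22–34% | 39–60% | 74–93% | 99–100% |
| 1,000 | 13–19% | 23–35% | 46–68% | 88–98% |
| 600 | 10–14% | 16–23% | 31–48% | 70–90% |

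Ranges run over event rates of 10–20%.

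**Effect on the technique contrast, first simulation.** 300 runs per setting, eight true confounders and ten null factors (prevalence 30% each), OR with technique 1.5, true technique OR 1.00, no matching and no institution effect.

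| Setting | Confounder OR | True confounders kept | Mean technique OR, p < 0.05 set | Mean technique OR, all factors |
|---|---|---|---|---|
| N = 2,000, rates 10–20% | 1.3 | 38–58% | 1.04–1.08 | 1.00–1.01 |
| | 1.5 | 72–91% | 1.01–1.04 | 1.00 |
| | 2.0 | 99–100% | 1.00 | 1.00 |
| N = 600, rate 15% | 1.3 | 18% | 1.10 | 1.00 |
| | 1.5 | 39% | 1.15 | 1.04 |
| | 2.0 | 78% | 1.07 | 1.02 |

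Full adjustment at N = 600 does not average exactly 1.00 in these runs. Relative to it, the drift is 1.096/0.995 = 1.10, 1.147/1.036 = 1.11 and 1.071/1.017 = 1.05. Across all settings the 5% test of technique rejected in 4–12% after selection and 3–7% with all factors (standard error about 1.3 points).

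**Second simulation.** 1,500 runs, confounders present in 25% versus 40% of the two groups, event rate about 8–10%, again without matching. With 400 per group, OR 1.5 confounders were missed in 59% of cases and OR 1.3 in 80%. With six OR 1.3 confounders the mean technique OR was 1.145 and rejection 8.5%, against 1.005 and 5.6% with full adjustment. With four confounders the OR was 1.06–1.09 and rejection 5–7%.

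**The case against.** The strongest reply is that no selection rule is written. The sentence does not say that variables are kept or dropped by p-value, does not name the dependent variable of this regression, and does not say that its result feeds any covariate set. The 0.05 level is a general closing statement. The phrase may be loose wording for adjustment, and a covariate list may properly sit in the full protocol or analysis plan. All of this stands, so the loss of confounders is conditional on a rule that the article does not state.

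Second, matching is planned in the same sentence and deals with the relation between covariates and technique. Neither simulation includes matching or the institution random effects, so neither describes the planned analysis. This also stands. The figures show what significance-based selection would do by itself.

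Third, part of the remedy is already present: candidate factors are those thought to influence outcomes, and each is to be discussed clinically. That helps, but a factor thought to influence outcomes may still follow the choice of technique.

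Fourth, flagging a purely prognostic factor as a confounder is common but harmless: adjusting for a factor unrelated to technique does not bias the contrast. No weight is placed on it here.

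The reply does not reach the stated purpose. Leaving a covariate list to another document is condensation. Saying that regression will find the confounders describes a method, and the method is the wrong one.

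**Conclusion.** The point holds as a correction to the stated method for the secondary technique comparisons. Regression cannot identify confounders, and the collected items include variables that come after the choice of technique.

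The size is conditional. If p < 0.05 decided which factors are kept, confounders with OR 1.2–1.3 would often be missed even with 2,000 patients (40–78% of the time). Most with OR 1.5 would be missed at about 600 patients, and at about 800 when the event rate is 8–10%. The null technique OR would average about 1.07–1.15 at N = 600 and 1.00–1.08 at N = 2,000. These figures rest on assumed event rates, prevalences and odds ratios, and leave out the planned matching.

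A reader might infer more, and the document does not support it:

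- That the plan drops confounders by p-value: no such rule is written.
- That most moderate confounders would be lost throughout: with 2,000 patients, 74–93% of those with OR 1.5 would be kept.
- That the comparisons will be biased: matching may remove much of what selection leaves, and this was not modelled.
- That intervals would be too narrow: this was not calculated.

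The primary incidence estimate is not affected.

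**What to change.** Replace the phrase on identifying confounders with wording such as:

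> *logistic regression adjusted for confounders prespecified on clinical grounds from preoperative items that precede the choice of technique; the same set enters the propensity score and the outcome model regardless of p-value, and intraoperative and postoperative variables are excluded.*

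Candidates already collected include age, body mass index, ASA-PS, ECOG-PS, comorbidities, tumour site, clinical T and N, preoperative obstruction, timing of surgery and laparotomy history. The list should be fixed before the short-term outcome data are analysed.

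The change needs wording only and no new data. The cost is slightly wider intervals, or a few more unmatched patients, in the small contrasts.

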**Methods:**

Patients undergoing laparoscopic or robot-assisted surgery for right-sided colon cancer at participating institutions in the Laparoscopic Colorectal Resection Study Group will be prospectively enrolled between 3 July 2024 and 31 May 2026. This multicenter study expects to enroll a total of 2,000 colorectal cancer cases from 73 facilities nationwide. The primary endpoint is the incidence of postoperative complications classified as Clavien–Dindo grade ≥ III. Risk factors contributing to these severe complications will be analysed. As a key secondary endpoint, the incidence and predictors of intraoperative vascular injury near the superior mesenteric vein will also be evaluated.

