**Fig. 1 Fig1:**
[figure not shown]
Questionnaire regarding the preferred approach for conventional laparoscopic right colectomy**.** A nationwide questionnaire was conducted in 2023 by the Japan Society of Laparoscopic Colorectal Surgery. The most preferred approach in each institution is shown. According to the survey, the medial and retroperitoneal approaches are the most preferred

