**Fig. 3 Fig3:**
[figure not shown]
Questionnaire regarding the preferred anastomosis for laparoscopic right colectomy. A nationwide questionnaire conducted in 2023 by the Japan Society of Laparoscopic Colorectal Surgery revealed institutional preferences for anastomosis techniques. (**a**) Extracorporeal anastomosis was predominant in conventional laparoscopic surgery, (**b**) while intracorporeal anastomosis was favoured in robot-assisted procedures

Given the above background, we have designed this prospective observational study to investigate factors influencing the safety of laparoscopic right-sided colon resection.

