### Selection criteria

Cases with a diagnosis of adenocarcinoma.Cases in which laparoscopic ileocecal resection, laparoscopic right hemicolectomy, or laparoscopic extended right hemicolectomy with D2 or D3 dissection are planned for clinical stage 0, I, II, or III colon cancer in the caecum, ascending, or transverse colon.Robot-assisted surgical cases will be eligible for inclusion only after the participating institution has demonstrated procedural proficiency through completion of at least 10 prior cases of ileocecal resection, right hemicolectomy, or extended right hemicolectomy for right-sided colon cancer.

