## Discussion

Successfully performing surgical procedures without intra- or postoperative complications is critical. A national survey in Japan demonstrated that the mortality rate of right hemicolectomy was higher than that of low anterior resection [7]. However, no detailed studies regarding the factors influencing the safety of this procedure have been conducted. Therefore, we will conduct the SCaRLET study to identify the rate and cause of severe perioperative complications in laparoscopic right-sided colectomy.

To the best of our knowledge, this will be the first large prospective study of laparoscopic right-sided colectomy in Japan, with nearly equal numbers of laparoscopic and robotic procedures. This study is characterised by a low event selection bias owing to its prospective nature. It will be conducted at Japanese institutions that excel in JSLCS, with high proficiency levels of performing laparoscopic and robotic surgeries. Hence, the institutional experience will not affect the study outcomes, potentially determining the actual safety of the procedure. We will investigate the actual incidence and causes of high mortality rates due to the procedure, which have not yet been clarified. Furthermore, we will investigate the actual incidence and causes of intraoperative vascular injury, which may be the only critical aspect in D3 lymph node dissection.

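### A random institution intercept alone does not protect the secondary technique comparisons from confounding by institution

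*Protocol article*

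**What the plan says.** Under Statistical analysis, the secondary-endpoint paragraph says of the subgroup contrasts in Table 1 that "group comparisons will be conducted after propensity score matching", with logistic regression alongside. Covariates are chosen "using the factors listed in the survey items that may influence outcomes". Institution is handled by one sentence: "A random-effects model will be used to account for the differences between institutions".

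The Background describes technique as something institutions hold. Of approach, the captions of Figs. 1 and 2 (laparoscopic and robotic) say "The most preferred approach in each institution is shown". The Fig. 3 survey "revealed institutional preferences for anastomosis techniques", with extracorporeal anastomosis predominant in laparoscopic surgery and intracorporeal favoured in robotic surgery. Platform was not surveyed. The nearest statement is in Selection criteria: "Robot-assisted surgical cases will be eligible for inclusion only after the participating institution has demonstrated procedural proficiency".

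The Abstract expects "2,000 colorectal cancer cases from 73 facilities nationwide". Institution type and annual volume are recorded. The Discussion adds: "Hence, the institutional experience will not affect the study outcomes".

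**The concern.** A random-intercept model treats each institution's deviation as noise unrelated to the covariates. If institutions that favour one technique also differ in case mix, perioperative care or readiness to treat, the technique odds ratio becomes a weighted blend of two contrasts: cases within the same institution, and institutions of different habit. Readiness to treat matters here because the main subgroup endpoint starts at grade II, which the definitions tie to giving medical therapy. The point estimate itself shifts; this is separate from getting the standard error right for clustering.

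The Background asks which approach and which anastomosis are safest. An institution difference could be read as part of the answer, from a model described as having dealt with institutions. The plan does not say that matching is done within institution, so matching as described does not settle the matter.

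**Working it through.** **The plan's own figure.** The only computed figure is the sample size, and this point does not touch it. 1.96² × 0.05 × 0.95 / 0.01² gives 1,825; the exact binomial interval averages ±1.0 point from about 1,940. At 2,000 the simple half-width is 0.96 points. The figure of about 2,000 stands.

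**Inputs.** From the document: K = 73 institutions and 2,000 cases, so m ≈ 2,000/73 ≈ 27 each. Assumed, because the document does not give them:
- grade ≥ II rate p = 15% (8% as an alternative)
- SD of institution log-odds 0.5 (alternative 0.3)
- half the institutions prefer each technique and use it in a share s of cases
- correlation ρ between institution risk and preference of 0, 0.3 or 0.5

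The true technique OR is 1 throughout.

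**Approximation, worked for s = 0.9, ρ = 0.5, SD 0.5.**
- Gap in mean log-odds between the two halves: d = SD × ρ × 2√(2/π) = 0.5 × 0.5 × 1.596 = 0.399.
- Within-institution information: K·m·s(1−s)·p(1−p) = 73 × 27 × 0.09 × 0.1275 = 22.6.
- Variance of the institution share: V = (s−½)² + s(1−s)/m = 0.16 + 0.0033 = 0.1633.
- Between-institution information: K·V / [SD² + 1/(m·p(1−p))] = 73 × 0.1633 / (0.25 + 0.2905) = 22.1.
- Between-institution slope: d(s−½)/(2V) = 0.399 × 0.4 / 0.3266 = 0.489.
- Random-intercept estimate: 0.489 × 22.1/(22.6 + 22.1) = 0.241, OR 1.27.
- SE: 1/√44.7 = 0.150, against 1/√22.6 = 0.210 for the within-institution estimate, a ratio of 1.40.
- False-positive rate: 0.241/0.150 = 1.61, so P(Z > 1.96 − 1.61) ≈ 36% against a nominal 5%.

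**Check by simulation.** Two separately programmed simulations fitted the random-intercept logistic model by maximum likelihood: A with unequal institution sizes (mean 27.4) and 800 replicates per setting, B with 27 cases each and 200 to 300 replicates. False-positive rates are in brackets.

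| Preferred use | ρ = 0.3: formula | ρ = 0.3: simulated | ρ = 0.5: formula | ρ = 0.5: simulated |
|---|---|---|---|---|
| 60% | 1.03 | B 1.03 (6%) | 1.04 | B 1.05 (6%) |
| 75% | 1.07 | A 1.07 (8%) | 1.13 | A 1.13 (14%) |
| 80% | 1.10 | B 1.09 (8%) | 1.16 | B 1.17 (17%) |
| 90% | 1.16 | A 1.17 (18%), B 1.15 (16%) | 1.27 | A 1.26 (34%), B 1.30 (40%) |
| 95% | 1.20 | B 1.21 (23%) | 1.36 | B 1.37 (51%) |
| 100% | 1.27 | B 1.27 (30%) | 1.49 | B 1.48 (65%) |

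At ρ = 0 the random-intercept OR is 0.98 to 1.01 with 4 to 6% false positives at every level of use. A negative correlation mirrors the bias (1/1.27 = 0.79).

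**What the random intercept removes.** At ρ = 0.5, ordinary logistic regression gives 1.09, 1.26, 1.37, 1.42 and 1.47 at 60, 80, 90, 95 and 100% use. The random intercept takes these to 1.05, 1.17, 1.30, 1.37 and 1.48: a real reduction with mixed use, almost none with near-exclusive use.

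**Other assumptions.** With an 8% rate and/or SD 0.3, ρ of 0.3 to 0.5 and 80 to 100% use, simulation B gives ORs of 1.06 to 1.49 with 7 to 51% false positives.

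**With the institution's technique share added.** The OR returns to 0.98 to 1.01 (5 to 6% false positives) in A and 0.97 to 1.04 (3 to 7%) in B, wherever institutions use both techniques. At 100% use the within-institution effect cannot be estimated.

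**The case against.** The strongest reply is that the quoted sentence is ordinary wording for modelling heterogeneity and clustering. The same paragraph assigns confounding to matching and regression, and institution type and volume can enter as covariates. The calculation above has neither matching nor institution covariates, so its odds ratios do not describe the full written plan. That stands, and it limits the size of the effect. It does not remove the point: type and volume do not capture unmeasured care or treatment thresholds, and the random effect is the only element whose stated purpose is to deal with institutions.

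A reader might infer that the model cannot adjust for institution at all, or that institution quality will be published as a technique effect. The document supports neither. The first is true only when technique is almost fixed by institution; the second needs a link between risk and preference that the document does not report. The surveys show the most preferred technique, not exclusive use, and nothing says their respondents are these 73 facilities.

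A reader might also extend the point to robot versus laparoscopy or to dissection level. No survey covers either; for platform there is only the institutional experience condition. Nor does it extend to the primary endpoint, which is an incidence. The same sentence appears in the primary paragraph, but nothing was calculated at the planned 5% rate.

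The analysis plan, not shown, may already contain a within-institution term. Its absence from the article is not the finding. The finding is that the stated model does not by itself secure the stated purpose for these exposures. The Discussion's assertion about institutional experience is no rebuttal, because it is assumed and not shown.

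**Conclusion.** The point holds for the secondary comparisons of approach and anastomosis: a random institution intercept alone leaves them open to confounding by institution. The size is unknown. Under the stated assumptions it runs from nil (no correlation) through OR 1.03 to 1.05 (60% preferred use) to about 1.15 to 1.3 at 90/10 use, where 16 to 40% of null comparisons would be significant at 0.05. These figures rest on an assumed event rate, institution SD, concentration of use and correlation, and take no credit for institution type and volume. It is a worthwhile and inexpensive improvement to secondary analyses and does not challenge the study's main estimate.

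**What to change.** Keep the random intercept and the institution covariates. In the mixed models comparing approach and anastomosis, add the institution's share of cases done with that technique, calculated among the cases in that comparison. Do the same for platform or dissection level if the data show use concentrated by institution.

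Report the within-institution and between-institution odds ratios separately, and state how many institutions use both techniques. Where the two disagree, do not describe institution as accounted for. Where few institutions use both, say that the within-institution effect is not estimable.

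The cost is one derived covariate per model, no new data, and a wider interval. At SD 0.5 the within-institution SE is about 9% larger at 75/25 use and about 40% larger at 90/10 (0.21 against 0.15). Those figures put all 2,000 cases in one contrast; the pairwise subgroups in Table 1 will be less precise. The within-institution estimate can still be confounded if the less-used technique is chosen by patient or surgeon, so it should be shown beside the other estimate and not used as the sole test of safety.
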